## 3. Discussion

This paper outlines the background and design of a randomized controlled trial that aims to determine the effectiveness of an 8-week exercise therapy program based on sports, combined with usual care, for ambulant adults with ABI, compared to usual care alone.

While previous studies reported positive results from implementing exercise therapy programs centered around sports such as basketball or soccer among people with physical disabilities [40], this study extends the scope of exploration on racket sports, specifically focusing on the ABI population.

A notable strength of this clinical trial lies in the multi-component nature of both the intervention design and assessments: (1) the program encompasses specific neurorehabilitation content alongside sports-based functional exercises that promote interactions and socialization among participants [19,21,40], and (2) the outcome measures involve a range of standardized scales and questionnaires that provide a comprehensive assessment of all the ICF domains [5,6].

As highlighted in earlier research, the proposed sport-based design emphasizes the importance of notably addressing the social domain within ABI rehabilitation, as the focus on the physical domain still predominates in this context. Further studies that integrate sport-based elements into their therapeutic approaches are needed to achieve higher levels of social inclusion within the functional rehabilitation field [9,21,41].

If this program proves effective, it will contribute to clinical practice implications for ABI rehabilitation, offering an evidence-based therapy option that emphasizes the social inclusion perspective and optimally addresses both physical and social recovery. In addition, the results of this study are expected to offer valuable guidance to multidisciplinary teams in achieving optimal levels of health-related quality of life and active lifestyles for their patients.

Finally, it is anticipated that the findings of the trial will be disseminated through peer-reviewed journals and presented at national and international conferences, contributing to broader knowledge and clinical practice in the field of ABI rehabilitation.

## Figures and Tables

**Figure 1 jcm-12-07068-f001:**
[figure not shown]
Flowchart of the study design.

**Table 1 jcm-12-07068-t001:** Eligibility criteria.

Inclusion Criteria	Exclusion Criteria
Persons with a medical diagnosis of an acquired brain injury in the subacute or chronic stage (within more than one month of the injury).	Do not have a completed and signed informed consent form.
Be aged >18 years at study entry.	Failure to attend and/or participate in 70% of the program sessions.
To walk independently without the use of assistive devices: score of ≥3, 4 or 5 on the Functional Ambulation Categories (FAC) walking test.	Have medical comorbidities that contraindicate safe exercise (e.g., cardiac or respiratory instability, and uncontrolled seizures).
Be able to understand simple instructions from the exercise therapy program and carry out baseline and post-intervention assessments.	Failure to cooperate during the preliminary tests of the program.

**Table 2 jcm-12-07068-t002:** Template for intervention description and replication checklist for the intervention.

TIDieR Items	Description of Items
Name of the intervention for experimental/comparison group	sET group: racket sports-based exercise therapy program. UC group: usual care
Rationale	Currently, several studies have been carried out that propose a program that combines exercise therapy and adapted physical activity based on different sports (such as basketball or soccer). Nevertheless, no racket sport-based program has been implemented so far. Racket sports emerge as an accessible therapeutic tool with a strong social component that enables the integration of different body synergies and complex motor strategies, thereby promoting functional performance in both the lower and upper limbs. To date, there remains a noticeable gap in the literature regarding exercise programs that comprehensively address all the domains of the International Classification of Functioning, Disability and Health model. This trial raises the need to specifically design exercise therapy programs based on racket sports for this population.
Materials used in the intervention	sET group: The exercise therapy program is centered around different racket sports skills, mainly badminton and tennis, as disciplines which are adapted to participants’ functional condition, as well as different generic equipment such as like balls, chairs, tables, and platforms, among others.
Intervention procedures	sET group: The content of this program is designed to synergize exercise therapy and sports elements. This approach facilitates transitioning from specific motor functional rehabilitation (first eight sessions) to more global skills based on racket sports (final eight sessions). UC group: Usual care encompasses a range of therapies (e.g., occupational therapy, physiotherapy, psychological support) provided by the rehabilitation services within the center. Following the post-intervention assessment, participants from this control group can participate in the same program sessions upon request.
Provider	sET group: The program will be delivered by a physiotherapist with expertise in neurological disorders and adapted physical exercise. UC group: Usual care for this group will be provided by professionals from the rehabilitation center.
Mode of intervention delivery	sET group: Presential, group-based sessions (from four up to six participants) to optimize the rates of social engagement. UC group: Presential, individual sessions.
Setting of intervention	Screening, interventions, and assessments will be conducted at the physiotherapy rooms of a rehabilitation center located in Madrid, Spain.
Dosage	sET group: Participants from this group will receive an 8-week exercise program which consists of sixteen sessions, 1 h session/day for 2 days/week. UC group: This group will continue with their usual care as usual 2 days/week, over 8 weeks and then will be reassessed.
Tailoring	The sessions content will be continuously tailored and adapted by a physiotherapist to meet the individual needs and functional levels of each participant, thereby ensuring precise execution and security.
Modifications	Not applicable.
Fidelity assessment	The therapist responsible for delivering and managing the intervention will conduct a phone follow-up every 2 weeks to monitor the adherence of the sET group to the program. Additionally, this professional will track the progress of participants from the UC group during these follow-up calls.

**Table 3 jcm-12-07068-t003:** Schedule of enrolment, interventions, and assessments from the SPIRIT guidelines.

	Study Period		
	Allocation	Post- Allocation	Completion
TIMEPOINT	T0	T1	T2
*ENROLLMENT:*			
Eligibility screen	X		
Informed Consent	X		
*INTERVENTIONS:*			
Sport-based Exercise Therapy Program + Usual Care			
Usual care			
*ASSESSMENTS:*			
Sociodemographic, anthropometric and comorbidity data		X	
Health-related quality of life (SF36)		X	X
Upper extremity motor function (FM-UE)		X	X
Functional capacity: gait endurance (6MWT)		X	X
Functional capacity: gait velocity (10MWT))		X	X
Mobility (TUG)		X	X
Balance (BBS)		X	X
Physical Activity (GPAQ)		X	X

SF36: Short-Form 36 Questionnaire; FM-UE: Fugl-Meyer Upper Extremity Assessment Scale; 6MWT: Six-Minute Walk Test; 10MWT: Ten-Meter Walk Test; TUG: Timed Up and Go Test; BBS: Balance Berg Scale; GPAQ: Global Physical Activity Questionnaire.

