### 2.3. Allocation and Blinding

After completion of the baseline assessment, independent, centralized, stratified block randomization will be used to allocate participants to either the intervention or the control group. Randomization will be performed using a computer-generated random number sequence, with a 1:1 allocation ratio. The assessors involved in eligibility, pre- and post-intervention assessments, and statistical analysis will be blinded to group allocation throughout the entire study period. Due to the nature of the trial, it is not possible to blind intervention parties, including both participant and program staff, to their group assignments.

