### 2.8. Sample Size

Based on a review of the literature [35,36], people who undergo an exercise therapy program show improvements such as improved quality of life and functionality. Therefore, the sample size was calculated based on the primary outcomes: SF-36 and FM-UE.

Previous studies have shown that a difference of 12.4 points with an SD of 5 points in the FM-UE score is required to detect the minimum clinically important difference between the two study groups [37,38].

Furthermore, Norman et al. conclude that the threshold for detecting changes in health-related quality of life is approximately 5 points [39]. Taking into account the possible number of subjects we could recruit, the sample size is calculated to detect an improvement of 5 points in the summary components of the SF-36 questionnaire with a standard deviation (SD) of 5 points. The SD value was taken as half that of the general population (SD = 10) because we considered our sample to be more homogeneous. To detect this difference between the groups with a 95% confidence interval and 80% power for a bilateral approach, we would need 16 subjects. If we estimated a 15% attrition rate, the final sample size would be 18 subjects in each group.

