### 2.10. Statistical Methods

The comparability of the study groups will be assessed by the similarity of the distribution of the variables of interest at baseline. The analysis will follow standard methods for randomized controlled trials, using two-group comparisons for all participants on an intention-to-treat basis. The chi-squared test or Fisher´s exact test will be used to compare proportions. Student´s *t*-test will be used to compare means between groups with normally distributed data. The Mann–Whitney test will be used to compare quantitative variables between groups in the case of a non-normal distribution, as determined by the Kolmogorov–Smirnov test. Correlations between quantitative measures will be determined by Spearman’s rho correlation coefficient. Matched pair data analysis is also calculated. In addition, multivariate analysis will be performed using multiple linear regression and logistic regression, depending on the response under consideration. This will allow for adjustment of the effectiveness of the intervention for potential confounders and the identification of other variables associated with each of the outcomes. Statistical significance will be set at ≤0.05. Data will be analyzed using the Statistical Package for the Social Science (SPSS) software, version 27.0 (IBM Corp, Armonk, New York, NY, USA).

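### Subacute and chronic participants are pooled, but the between-group test stated in the plan takes no covariate, so any recovery that differs by stage stays in its error term

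*Protocol article*

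**What the plan says.** All references are to the protocol article.

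- **Population.** Table 1 admits "Persons with a medical diagnosis of an acquired brain injury in the subacute or chronic stage", more than one month after injury, and sets no upper limit. Section 2.2 also names both stages.
- **Allocation.** Section 2.3 states that "independent, centralized, stratified block randomization will be used to allocate participants". It does not name the stratification factors.
- **Comparison.** Section 2.10 describes the analysis as "using two-group comparisons for all participants on an intention-to-treat basis". Student's t "test will be used to compare means between groups with normally distributed data", and the Mann-Whitney test is used otherwise. Multiple linear and logistic regression come in addition, to adjust for potential confounders that are not named and to find other variables associated with the outcomes. No analysis is labelled primary.
- **Baseline data.** Section 2.6.3 lists date of birth, sex, school type, weight, height, diagnoses and comorbidities. It does not list time since injury or stage.
- **Sample size.** Section 2.8 uses a 5-point difference in the SF-36 summary components with SD 5, which is half the general-population SD of 10, "because we considered our sample to be more homogeneous". It arrives at 16 per group, or 18 after attrition. For FM-UE it gives a difference of 12.4 points with SD 5.

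**The concern.** A participant several weeks after injury may improve over an 8-week interval in either arm, while one several years after injury may be stable. The plan draws this distinction at entry but uses it in no stated analysis. A two-sample t-test or Mann-Whitney test cannot take stage into account, so any difference in recovery between stages is treated as noise. With 18 per group there is little room for avoidable noise.

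The sample-size argument makes this sharper. It halves the SD because the sample is taken to be homogeneous, while eligibility is wide on a characteristic that may well predict change.

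At stake is the precision of the SF-36 comparison, which determines the size of the trial.

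**Working it through.** **Step 1: reproduce the planned size.** Inputs from sections 2.8 and 2.10: difference 5, SD 5, two-sided alpha 0.05, power 80%.

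n per group = 2 × (1.960 + 0.842)² × 5² / 5² = 15.7, so 16. This matches the plan and confirms that the size rests on an unadjusted two-sample comparison. By the exact t-test (noncentrality (5/5) × √(16/2) = 2.83, 30 degrees of freedom), power at 16 per group is 78.1%. The gap between 78% and the stated 80% comes from the normal approximation and has nothing to do with stage.

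**Step 2: assumptions the article does not supply.** Let q be the subacute share (one third or one half), and D the extra change in subacute participants whatever their arm (2.5, 5 or 10 SF-36 points). The between-stage variance is D² × q(1−q).

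**Step 3: reading A, SD 5 is the within-stage SD.** Total SD = √(25 + D² q(1−q)). Power is for 5 points at 16 per group, exact t-test.

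| D | q | Between-stage variance | Total SD | Power |
|---|---|---|---|---|
| 0 | – | 0 | 5.00 | 78% |
| 2.5 | 1/3 | 1.39 | 5.14 | 76% |
| 2.5 | 1/2 | 1.56 | 5.15 | 76% |
| 5 | 1/3 | 5.56 | 5.53 | 70% |
| 5 | 1/2 | 6.25 | 5.59 | 69% |
| 10 | 1/3 | 22.2 | 6.87 | 51% |
| 10 | 1/2 | 25.0 | 7.07 | 49% |

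Under this reading, adjusting for stage brings the SD back towards 5.

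**Step 4: reading B, SD 5 is already the total SD of the mixed sample.** Unadjusted power stays at 78%. Adjustment removes the between-stage part, so the residual SD = √(25 − D² q(1−q)):

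- D = 2.5: √23.6 to √23.4, about 4.9 to 4.8. Power is about 80–81%.
- D = 5: √19.4 to √18.75, about 4.4 to 4.3. Power is about 87–88%.
- D = 10 does not fit this reading. At q = 1/2 the between-stage variance of 25 would use up the whole planned variance.

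**Step 5: FM-UE.** The stated difference is 12.4. Even at the largest SD in the table, 7.07, noncentrality is (12.4/7.07) × √8 = 4.96, and power at 16 per group is above 99%.

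**Step 6: price of the adjustment.** Two model terms take the error degrees of freedom from 30 to 28. If both terms explained nothing, power at SD 5 would go from 78.1% to 77.9%.

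**The case against.** The strongest reply has four parts.

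1. **The article does not show that stage goes unused.** Allocation is stratified and a regression is planned. Stage could be a stratum or a covariate, and an article may leave such detail to the full protocol. This stands as far as it goes. A reader might infer that randomisation ignores stage, but the article supports neither that nor the opposite. If stage were not a stratum, and 12 or 18 of 36 participants were subacute, the arms would differ by 4 or more subacute participants in 29% or 32% of allocations. That figure is conditional and is not part of the finding. The planned regression does not settle the matter, because it is added to the covariate-free tests rather than replacing them. Even if stage is a stratum, those tests leave its variance in the error term.

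2. **SD 5 is given for the sample as a whole.** On that reading stage costs no planned power. This is fair, and it is why both readings are shown. The loss then takes another form: precision that is available but not taken.

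3. **The recovery differences are assumed.** Differences of 5 to 10 points are one to two times the target effect, and entry is limited to outpatients who walk without aids, which may narrow the spread. This also stands. At 2.5 points the loss is only about two percentage points of power.

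4. **Chance imbalance and added variance are the same random error.** This is correct. Without stratification by stage, imbalance would shift the estimate with an SD of about 0.8 to 1.7 points (0.159 × 5 to 0.169 × 10). That shift is already part of the standard error behind the power figures. It is neither a second harm nor a bias.

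Likewise, the absence of time since injury from section 2.6.3 does not prove that it goes unrecorded, since eligibility cannot be checked without it.

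**Conclusion.** The point holds as one of precision in the SF-36 comparison. The article fixes a covariate-free test for a population that it defines as mixed in stage, and leaves adjustment to a supplementary regression with no covariates named.

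The size cannot be determined from the article. On the assumptions above it runs from a loss of about two percentage points of power (2.5 points between stages) to 49–51% power (10 points) if SD 5 is within-stage. If SD 5 is the total, nothing is lost against the plan, but a gain of about 2 to 10 percentage points is forgone for stage differences of 2.5 to 5 points. FM-UE is not at risk on the plan's own figures.

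The article does not support a claim of bias, of randomisation known to omit stage, or of a trial certain to fall short of 80% power because of stage. The change is worth making because it is nearly free, not because a large loss has been shown.

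**What to change.** - In section 2.6.3 and Table 3, add time since injury to the data recorded at T1.
- In section 2.10, make the primary comparison for SF-36 and FM-UE a linear model of the T2 score on treatment, baseline score and stage, in place of the unadjusted t-test or Mann-Whitney test. Stage is subacute versus chronic, with the sponsor's own cut-off fixed in advance. Include any factor used to stratify the randomisation. The unadjusted test can be kept as a supporting analysis.

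**Cost.** One recorded variable, which screening already requires, and two degrees of freedom (baseline score and stage). Each further stratification factor costs at least one more. No extra participants, visits or procedures are needed.

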### 2.2. Eligibility and Recruitment

The study population consists of outpatients aged 18 years and over with a confirmed diagnosis of subacute or chronic acquire brain injury. A summary of the eligibility criteria is given in Table 1. Recruitment will take place over a period of 3 months to ensure that the target sample size is achieved. Potential patients from the rehabilitation center database will be invited to participate in the study through site visits and telephone calls. Eligibility will be established through prospective face-to-face interviews and eligible individuals will then be enrolled into the study. Throughout this process, participants will provide a signed written informed consent indicating their understanding of the objectives and requirements of the study.

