### 2.4. Interventions

Exercise therapy program based on racket sports (sET):

Participants in the sET group will participate in an exercise therapy program based on racket sports, combined with their usual care sessions as usual. The program will be delivered over sixteen 60 min sessions, delivered twice a week for 8 weeks. The sessions will be delivered in a group format of four to six participants to optimize social engagement rates.

Session content will be carefully designed based on the motor patterns associated with racket sports, allowing for a progressive and effective transition from specific motor function training to broader sports-related tasks. Exercises are continuously tailored and adapted by a physiotherapist in order to meet the individual needs and functional level of each participant, ensuring accuracy and safety. The Template for Intervention Description and Replication (TIDieR) checklist was used to ensure complete reporting of the intervention (Table 2) [27].

Usual care (UC):

Participants in the UC group will continue to receive their usual care for the duration of the study and will be reassessed. Usual care includes a range of therapies (e.g., occupational therapy, physiotherapy, psychological support) provided by the rehabilitation services within the center. After the post-intervention assessment (T2, 2 months after the intervention), participants in this group will have the opportunity to attend the same program sessions if they wish.

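### A 70% attendance rule listed as an exclusion criterion can act only after randomization and only on the sET arm, which contradicts the stated intention-to-treat analysis

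*Protocol article*

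**What the plan says.** Table 1 (Eligibility criteria) gives as one of four exclusion criteria: "Failure to attend and/or participate in 70% of the program sessions".

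Section 2.2 places the eligibility decision before entry: "Eligibility will be established through prospective face-to-face interviews and eligible individuals will then be enrolled into the study". Section 2.3 places randomization next: "After completion of the baseline assessment, independent, centralized, stratified block randomization will be used to allocate participants".

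Section 2.4 describes the program given to the sET arm: "The program will be delivered over sixteen 60 min sessions, delivered twice a week for 8 weeks". For the comparator it says: "Participants in the UC group will continue to receive their usual care for the duration of the study and will be reassessed". Only after the T2 assessment is the program open to the control arm, when "participants in this group will have the opportunity to attend the same program sessions if they wish".

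Table 2 (Fidelity assessment) provides fortnightly calls "to monitor the adherence of the sET group to the program". The same calls follow the progress of UC participants, with no mention of attendance for them.

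Section 2.10 defines the analysis as "using two-group comparisons for all participants on an intention-to-treat basis". Section 2.7 says that all participants attend baseline and are re-assessed at 8 weeks (T2).

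Nowhere does the article describe the 70% figure as an adherence definition or a per-protocol threshold. Nor does it say that people who fall below it stay in the analysis.

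**The concern.** An exclusion criterion should be decidable before randomization. This one depends on behaviour during the 8 weeks that follow, so it can work only as a rule for removing people already randomized. It is also one-sided. A UC participant who would have attended poorly cannot be identified before T2 and stays in, while the counterpart in sET goes out.

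Randomization makes the two arms comparable as allocated. Removing a self-selected subset from one arm gives that up, and baseline adjustment does not reliably restore it, because the reasons for missing sessions are only partly measured. The rule decides who enters the comparison on both primary outcomes (SF-36 and FM-UE), in a trial with 18 people per arm.

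**Working it through.** **Step 1. When can the rule be applied?**

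| Event | Source | Timing |
|---|---|---|
| Eligibility interview, enrolment | Section 2.2 | before randomization |
| Baseline assessment | Sections 2.3 and 2.7 | before randomization |
| Randomization 1:1 | Section 2.3 | after baseline |
| Sixteen program sessions (sET only) | Section 2.4, Table 2 | 8 weeks after allocation |
| T2 assessment | Section 2.7 | end of the 8 weeks |
| Optional program for UC | Section 2.4, Table 2 | after T2 |

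The threshold is 0.70 × 16 = 11.2 sessions, so 12 or more meets it and 11 or fewer fails. Whether someone has failed cannot be known before randomization. No UC participant can fail before T2, because UC has no program sessions until then.

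**Step 2. Do the rules agree?** Take an sET participant who attends 10 of 16 sessions. Under Table 1 this person is excluded. Under section 2.7 this person is re-assessed at T2, and under section 2.10 is analysed. Read literally, the rules give different answers for the same person.

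**Step 3. The plan's own sample size (section 2.8).** With difference 5, SD 5, two-sided 5% and 80% power, n per arm = 2 × (1.96 + 0.8416)² × (5/5)² = 15.70, rounded up to 16, as stated. For 15% attrition, 16 × 1.15 = 18.4 and 16/0.85 = 18.8. The stated 18 per group is within rounding of both. These figures serve only as inputs to step 4.

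**Step 4. How large could the effect be?** The article gives neither the share of poor attenders nor their outcomes, so both are assumed.

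- p = share of participants, in either arm, who would attend poorly.
- D = amount by which their outcome is lower, whichever arm they are in.
- No true treatment effect; m = mean outcome of good attenders.

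UC keeps everyone, so its mean is m − pD. sET after removal has mean m. The apparent effect is m − (m − pD) = **p × D**.

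Type I error was found by simulating a two-sample t-test with 16 per arm, total SD 5 and poor attenders removed from sET only:

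| p | D = 0 | D = 2.5 (half an SD) | D = 5 (one SD) |
|---|---|---|---|
| 10% | bias 0; 0.05 | bias 0.25; 0.051 | bias 0.5; 0.056 |
| 20% | bias 0; 0.05 | bias 0.50; 0.057 | bias 1.0; about 0.08 |
| 30% | bias 0; 0.05 | bias 0.75; about 0.065 | bias 1.5; 0.11 to 0.12 |

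Against the 5-point target, the biases run from 0.25/5 = 5% to 1.5/5 = 30% of the planned effect. With 18 per arm and D = 5 the error rates are slightly higher: about 0.06, 0.08 and 0.12.

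A second model, with 18 per arm, removed the 3 to 6 lowest attenders from sET and set the attendance–outcome correlation at 0.3 to 0.5. It gave a bias of about 0.4 to 1.3 points and a type I error of about 0.06 to 0.11. With zero correlation there was no bias. Keeping all 18 per arm held the error at 0.05.

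**The case against.** The strongest reply is that Table 1 never says poor attenders leave the analysis. The only explicit statement about the analysis set is in section 2.10, and it says all participants; section 2.7 says the same of T2. The attendance line may simply be an adherence or withdrawal rule put in the wrong table. That is a fair reading of intent, and it means a plan to analyse a depleted sET arm is not established. It does not remove the conflict: an exclusion criterion normally has an effect, and nothing in the article limits this one to something harmless.

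It might also be said that analysis sets belong in a statistical analysis plan. That would answer a missing detail. Here the protocol states a rule, and the rule contradicts another.

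Three stronger readings are tempting but unsupported:

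- **That the rule certainly favours sET on both primary outcomes.** This needs poor attenders to do worse on both SF-36 and FM-UE, and the article is silent on that. If higher-functioning people miss sessions, for instance because they are working, the sign reverses. The illustration covers SF-36 only.
- **That removals would exceed the 15% attrition allowance.** Section 2.8 does not define attrition, so the 15% may already include people lost under this rule. No non-attendance rate is given either.
- **That type I error is seriously inflated.** This holds only when poor attenders are both common and much worse off. At half an SD, the rate stays between about 0.05 and 0.07.

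**Conclusion.** The point stands as a contradiction that must be resolved before analysis. As written, Table 1 contains a post-randomization exclusion that can touch only sET, and it cannot be applied alongside sections 2.7 and 2.10. Following it would give the wrong analysis set for the primary comparison.

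The contradiction follows from the text alone. The size of any bias does not: it is p × D under the assumed model, roughly 0.25 to 1.5 SF-36 points for p of 10% to 30% and D of 2.5 to 5, and zero if attendance is unrelated to outcome. A bias toward sET is plausible but rests on the assumption that poor attenders do worse in either arm.

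**What to change.** 1. Remove the attendance line from the exclusion criteria in Table 1.
2. Add a sentence to section 2.10, consistent with section 2.7: every randomized participant is assessed at T2 whatever their attendance, and is analysed in the assigned arm in the primary analysis.
3. Keep the 70% threshold (12 or more of 16 sessions) only as a definition of adherence. If an analysis by adherence is wanted, label it supplementary; it is optional.

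The cost is one line moved and one sentence added. No extra participants or visits are needed, since section 2.7 already plans T2 for everyone.

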### 2.5. Harms

Risk assessment and mitigation strategies will be analyzed and implemented both before and during the trial. Safety and adverse events associated with the groups will be monitored throughout the intervention and reported to the ethics committees if serious. All identified unintended effects or adverse events will be recorded by the research team according to standard guidelines and reported to the ethics committee.

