In addition, a physiotherapist will conduct a comprehensive clinical examination to determine whether participants have any physical conditions that may affect their ability to perform certain activities and require adaptations. Participants in both groups will also complete an exercise diary documenting the duration, type and modality (aerobic, strength, flexibility) of their session, which will serve as an additional measure.

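### Harm counts by arm are open to differential detection: the trial contacts described differ between sET and UC, and no common way of eliciting adverse events is named

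*Protocol article*

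**What the plan says.** Section 2.5 (Harms) covers both arms: "Safety and adverse events associated with the groups will be monitored throughout the intervention and reported to the ethics committees if serious". It adds that the research team logs the events that are identified. It does not say how events are to be found, at which contact, or by whom they are asked about.

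The contacts that could bring an event to light are described elsewhere:

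- **sET sessions.** Section 2.4 gives "sixteen 60 min sessions, delivered twice a week for 8 weeks", and Table 2 (Provider) has a physiotherapist deliver them.
- **Calls.** Table 2 (Fidelity assessment) says of sET: "The therapist responsible for delivering and managing the intervention will conduct a phone follow-up every 2 weeks to monitor the adherence of the sET group". Of the other arm it says "this professional will track the progress of participants from the UC group during these follow-up calls".
- **Usual care.** Table 2 (Dosage) says of UC: "This group will continue with their usual care as usual 2 days/week, over 8 weeks and then will be reassessed". The Provider row adds: "Usual care for this group will be provided by professionals from the rehabilitation center". Section 2.4 says sET participants keep their usual care too, without giving its frequency.
- **Assessments.** Section 2.7 has T1 and T2 in both arms. Section 2.3 blinds the assessors but not the program staff.
- **Diary.** Section 2.6.2 says "Participants in both groups will also complete an exercise diary documenting the duration, type and modality (aerobic, strength, flexibility) of their session". Adverse events are not among the listed contents.

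**The concern.** A log of identified events depends on the chances to identify them. Only sET participants are watched during exercise by trial personnel, 16 times. Between T1 and T2, the one scheduled trial contact that both arms share is the fortnightly call. Its stated purpose differs by arm (adherence or progress), and in neither arm is it harms. The caller knows the allocation and delivers the program under test.

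Two forces could then act on the recorded counts. More supervised contact may raise them in sET. Collection by the person who delivers sET may lower them. Because the net direction is unknown, raw counts cannot be corrected afterwards.

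The stake is the safety reading of a new program. Table 2 (Rationale) says that no racket-sport program has been implemented so far. Section 2.8 plans 18 participants per group, so one extra participant with a recorded event shifts an arm's proportion by 1/18 = 5.6 percentage points.

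**Working it through.** **Inputs**

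- Sessions: 2 per week for 8 weeks (Section 2.4).
- Calls: one every 2 weeks (Table 2, Fidelity assessment), taken as the same schedule in both arms.
- Assessments: T1 and T2 in both arms (Section 2.7).
- Usual care in UC: 2 days per week for 8 weeks (Table 2, Dosage). The frequency in sET is not given, and 16 visits are assumed.

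**The plan's own figure.** 2 × 8 = 16 sessions, as stated.

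**Calls.** 8 / 2 = 4 per person, or 3 if none falls at week 8.

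**Contacts per person**

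| What is counted | sET | UC | Ratio |
|---|---|---|---|
| Sessions and 4 calls | 16 + 4 = 20 | 4 | 5.0 |
| The same with 3 calls | 16 + 3 = 19 | 3 | 6.3 |
| The same with 4 calls, 70% of sessions attended | 11.2 + 4 = 15.2 | 4 | 3.8 |
| Sessions, 4 calls, T2 | 21 | 5 | 4.2 |
| Sessions, 4 calls, T1 and T2 | 22 | 6 | 3.7 |
| Sessions, 4 calls, 16 usual-care visits (assumed in sET) | 36 | 20 | 1.8 |

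At full attendance the difference is 16 contacts in every row, all in sET. The ratio depends on what is counted as a contact.

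**What this could do to counts (illustration only).** Suppose each contact independently reveals a given event with the same probability q. With k contacts, the chance of recording it is 1 − (1 − q)^k. The document gives no value for q, so a range is shown. With equal true event rates, the apparent sET/UC ratio is:

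| q | 20 v 4 contacts | Ratio | 36 v 20 contacts | Ratio |
|---|---|---|---|---|
| 0.02 | 33% v 8% | 4.3 | 52% v 33% | 1.55 |
| 0.05 | 64% v 18% | 3.5 | 84% v 64% | 1.31 |
| 0.10 | 88% v 34% | 2.6 | 98% v 88% | 1.11 |
| 0.20 | 99% v 59% | 1.7 | 100% v 99% | 1.01 |
| 0.50 | 100% v 94% | 1.1 | 100% v 100% | 1.00 |

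The apparent ratio thus runs from 1.0 to 4.3, according to q and to whether events noticed at usual-care visits reach the research team. The document settles neither. The model also leaves out any effect of the unblinded caller, which could act the other way.

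**Restricting the comparison to contacts both arms share.** 4 calls + T1 + T2 = 6 in each arm, a ratio of 1.0.

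**The case against.** The strongest case on the other side has four parts.

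1. *No route of ascertainment is stated.* Section 2.5 names none, and the calls are listed as a fidelity check. This stands: a reader might infer that harms are collected through 20 contacts in sET and 4 in UC, but the document does not say so. An article may also leave the detail of elicitation to a fuller protocol. That does not dispose of the point, because the article itself fixes the caller, the frequency and an arm-specific purpose for the calls.

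2. *A five-fold gap is selective.* UC participants attend the same center about 16 times for usual care, and both arms have T1 and T2. This stands too. Usual-care staff are not said to report events to the trial, but neither is the session physiotherapist. Five-fold is one end of the counts, not a measure of bias.

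3. *No comparison of harms is planned.* Section 2.10 does not name harms, and they are not among the outcomes in Section 2.6. So it goes too far to say that a planned between-group harms analysis is biased. Events are nevertheless monitored in both groups, and counts by arm will be read against each other whether or not they are tested.

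4. *Extra supervised contact is inherent in an add-on design.* True, and the sessions themselves are not a fault. What can be equalized is the way events are asked about.

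**Conclusion.** The point holds as a risk built into the contacts described, not as a demonstrated bias. Identified adverse events are logged in both arms with no common method of elicitation named. sET adds 16 supervised contacts, and the shared calls are made by the unblinded sET therapist with a different stated purpose in each arm. Harm counts by arm can differ through detection alone.

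The contact counts are 20 versus 4 for trial-specific contacts, 22 versus 6 with T1 and T2, and about 36 versus 20 when usual-care visits are added to the trial-specific count. These rest on four calls per person, full attendance and, for the last, 16 usual-care visits in sET. A reader might go on to infer that sET harms will be over-recorded by some stated factor. The document does not support that: it gives no detection probability, does not say whether usual-care staff report events, and leaves even the net direction open.

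This is a cheap improvement worth making before data collection, not a flaw that undermines the trial's primary outcomes.

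**What to change.** - Put one identical, scripted set of adverse-event questions in the fortnightly calls already planned for both arms (for example falls, new pain, seizure, other illness, any medical contact).
- Have the blinded assessor repeat the same questions at T2. Ask them after the outcome measures are complete, since an answer may reveal the arm.
- Add a matching item to the exercise diary that both arms already keep.
- Use these systematically elicited events as the like-for-like comparison by arm, and count any event reported there even if it happened at an sET session.
- In a second table, report all events by arm from every source. Flag those observed only at sET sessions by source and do not exclude them: leaving them out could hide harm caused by the intervention.

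The cost is a few minutes per call, changes to the call script and diary wording, and a second harms table. No new visits or staff are needed. One limitation remains: the caller is still unblinded. A fixed script limits that influence without removing it; having the calls made by someone who does not deliver sET would reduce it further, if staffing allows.
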